#### Acceptance and preference.

This focuses on understanding how PwPD accept and prefer personalised music cues over metronome cues for gait retraining. It involves gathering subjective feedback on the likeability, engagement, and perceived effectiveness of the music cues, especially in contrast with the metronome cues. Preference of musical cues will influence long-term adherence to a cueing intervention. This also includes investigating which cue is found to be the easiest to adhere to, as well as the results from the SUS questionnaire.

#### Adherence to cues and musicality.

Adherence will be treated both as a continuous variable (percentage change in cadence from baseline) and as a binary variable for group comparisons. The primary binary adherence definition is: adherent = ≥5% increase in cadence from baseline; non-adherent = < 5%. Mann–Whitney U tests will compare Gold-MSI between adherent and non-adherent participants. Participants with missing baseline or intervention-based cadence (e.g., wishing to withdraw or technology failure) will be excluded from binary adherence analyses and numbers excluded will be reported.

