#### Walking/gait tasks.

Participants will choose from a selection of music tracks that span genres including pop, rock, R&B, and country. All walks will be 1-minute in duration in a continuous 25m loop, including two 8.5m straight segments and two 4m turns, Fig 3. Walk #1 will be at the participant’s natural walking pace to calculate a baseline cadence, i.e., a walk with no cueing (NC). Walks #2, #4, and #6 will be cued, with external auditory stimuli (BPM set at +10% of baseline cadence) which are metronome (Me), instrumental music (IM), and vocal music (VM). Participants will be assigned to one of three counterbalanced cue sequences for Walks #2, #4, and #6. For example, the first participant enrolled to the study follows Sequence 1, the second follows Sequence 2, the third follows Sequence 3, and the fourth cycles back to Sequence 1, etc.

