### Statistical analysis

For the first primary objective, all gait characteristics derived from CuePD and reference will be compared using ICC_2,1_ (absolute agreement), a two-way random-effects model for single measures that evaluate the absolute agreement between raters. The level of agreement will be interpreted as: < 0.5 shows poor agreement, 0.5–0.75 moderate, 0.75–0.9 good and 0.9–1.0 excellent. PCC’s will be calculated to measure the linear correlation between the two sets of results. Correlation coefficients will be interpreted as follows: zero (0), weak (±0.1 to ±0.3), moderate (±0.4 to ±0.6), strong (±0.7 to ±0.9), and excellent/perfect (+1 or −1).

The median, mean, standard deviation (SD), minimum/min, maximum/max, and standardised response mean (SRM) of cadence, stride length, gait speed and CV_stride-time_ will be calculated. These descriptive statistics will provide context for interpreting changes and help to clarify the magnitude and consistency of cueing effects. SRM allows for assessment of responsiveness and comparison of results to other studies. The SRM will be interpreted as: > 0.8 large positive response, 0.5–0.8 moderate responsiveness, and <0.5 low responsiveness where positive values imply an improvement for cadence, gait speed and stride length but negative is an improvement for CV_stride-time_, i.e., reduces variability.

To evaluate the cueing modality adherence, the percentage change in cadence from the baseline walk to each cueing modality will be calculated for each participant. The most effective cueing modality will be identified as the one producing a change closest to 10%.

Model assumptions will be formally checked, where residual normality and normality of gait characteristics within each cue condition will be assessed using the Shapiro-Wilk test, and sphericity with Mauchly’s test. The Greenhouse-Geisser correction will be applied if sphericity is violated.

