To evaluate the relationship between musical sophistication and response to cueing, two sets of analyses will be conducted using Gold-MSI subscale scores. Assumption checks, including the Shapiro-Wilk test and Q-Q plot inspections, will be used to assess the distribution of change scores prior to both analyses. First, the association between Gold-MSI scores and cue adherence (defined as the absolute deviation from a + 10% target increase in cadence) will be assessed using Spearman’s rank correlation coefficient, with Bonferroni correction for multiple comparisons across subscales. Second, associations between Gold-MSI scores and gait outcome improvements (percentage change in gait speed and stride length, and log-ratio change in ${\text{CV}}_{\text{stride}-\text{time}}$) will also be tested using Spearman’s correlation, with Bonferroni correction.

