### Exploratory objectives: preference, usability, and musicality

Exploratory objectives of the protocol also focus on the user experience and the clinical efficacy of the personalised auditory cues provided by CuePD. A significant part of this exploration involves understanding the preferences of PwPD for engaging with personalised music cues during routine walking exercises, compared to traditional metronome cues which are often perceived as monotonous and less engaging. This preference for music could play a crucial role in enhancing patient engagement and adherence to the rehabilitation process. Finally, the study explores how well patients’ musicality correlates with their ability to synchronise with the auditory cues. If no relationship is found, this would indicate that the success of music cueing-based interventions does not depend on a patient's inherent musical skills, potentially broadening the applicability of such treatments to a wider demographic of PwPD.

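### The two musicality analyses score cue adherence by incompatible rules, one of which credits overshoot, and a null result is given a reading that 54 to 60 participants cannot support

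*Protocol article*

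**What the plan says.** All places are in the protocol article.

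- **Target.** Under Walking/gait tasks the cued walks have "BPM set at +10% of baseline cadence", and the instruction for each is to walk to the beat.
- **Outcome measures, Adherence to cues and musicality.** "Adherence will be treated both as a continuous variable (percentage change in cadence from baseline", and also as a binary variable. The primary binary rule is "adherent = ≥5% increase in cadence from baseline". No upper limit is given. The test is: "Mann–Whitney U tests will compare Gold-MSI between adherent and non-adherent participants".
- **Statistical analysis, Gold-MSI paragraph.** Here adherence is the "absolute deviation from a + 10% target increase in cadence". It is related to Gold-MSI by Spearman's correlation, with Bonferroni correction across the subscales.
- **Statistical analysis, modality ranking.** Percentage change is computed for each participant and cue, and then "The most effective cueing modality will be identified as the one producing a change closest to 10" per cent.
- **Discussion, Exploratory objectives.** "If no relationship is found, this would indicate that the success of music cueing-based interventions does not depend on" a patient's musical skill. The text adds that this might widen the applicability of such treatment.

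**The concern.** Following a beat set at +10% means matching it. Absolute deviation from +10% measures that. Signed change and an open-ended threshold of 5% measure something else, namely how far cadence rose. Both kinds of score carry the name adherence, and both feed a test against Gold-MSI for secondary objective (b). The Mann–Whitney and Spearman results can therefore point in different directions, and the article does not say which one answers the objective.

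Two related points sit beside this. The rule for the most effective cue looks at closeness of a change to 10%, which may hide scatter between participants. And the Discussion attaches a substantive meaning to a null musicality result, although the only sample-size calculation concerns gait speed.

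**Working it through.** **1. The rules applied to the same participants.** Score A is the class under the 5% threshold. Score B is |change − 10|.

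| Cadence change | A | B (points) |
|---|---|---|
| −5% | non-adherent | 15 |
| 0% | non-adherent | 10 |
| +5% | adherent | 5 |
| +10% | adherent | 0 |
| +20% | adherent | 10 |
| +25% | adherent | 15 |

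The +20% and 0% walkers tie on B and are split by A. So do +25% and −5%. A is therefore not a cut of B.

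**2. How much overshoot.** The document gives no distribution of cadence change, so these are assumptions. For change ~ Normal(mean, SD), the share of adherent participants above +15% is P(change > 15) / P(change ≥ 5).

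- Mean 5, SD 4: 0.006 / 0.500 = about 1%.
- Mean 8, SD 4: 0.040 / 0.773 = about 5%.
- Mean 10, SD 6: 0.202 / 0.798 = about 25%.

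The rank correlation between signed change and closeness to +10% (minus B) is about 0.96, 0.6 and 0 in these three cases. The conflict thus runs from trivial to complete.

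**3. Can the musicality answer change?** Assume that musicality narrows scatter, with SD of cadence change = 6 × exp(−0.4 × musicality z-score), and simulate 200,000 participants.

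| Mean change | rho with B | rho with signed change | Mann–Whitney AUC under A |
|---|---|---|---|
| +10% | −0.39 | 0.00 | 0.65 |
| +8% | −0.34 | 0.00 | 0.59 |
| +5% | −0.20 | 0.00 | 0.50 |

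In the last row the same data show a relationship under B and none under A.

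**4. Cue ranking.** The article does not say how participants are combined. If changes are averaged first, a cue with half at −5% and half at +25% has mean (−5 + 25)/2 = 10%, a perfect score, with mean absolute deviation 15 points. It beats a cue with everyone at +8%, whose deviation is 2 points.

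**5. What a null can show.** No power is stated for musicality, so there is no figure to reproduce. Inputs: 60 recruited and 10% attrition (Sample size section), so 60 × 0.90 = 54. Five subscales give alpha 0.05/5 = 0.01, two-sided (critical value 2.576). By Fisher's z, SE = √(1.06/(n − 3)), which is 0.144 at n = 54 and 0.136 at n = 60. Power per test = 1 − Φ(2.576 − atanh(rho)/SE).

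- rho 0.3: atanh = 0.3095. Ratios 2.147 and 2.270 give 33% and 38%.
- rho 0.4: atanh = 0.4236. Ratios 2.939 and 3.107 give 64% and 70%.
- rho 0.5: 89% and 93%.
- 95% interval around an observed rho of 0: ±tanh(1.96 × SE) = ±0.28 and ±0.26.

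Adding the general score (six tests) gives 31% to 36% at rho 0.3. With no correction it is 57% to 62%.

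**The case against.** Several things can fairly be said for the plan. Keeping a continuous and a binary version of an outcome is not an error in itself. A one-sided threshold fits the stated aim of raising cadence, and the Statistical analysis section treats a positive cadence change as an improvement. Anyone at or below +10% is ranked identically by signed change and by deviation, so the rules part only through overshoot, whose frequency is unknown. All of this stands. It limits the size of the problem, but it does not make a rise in cadence and closeness to the beat the same quantity.

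A reader might also infer more than the document supports:

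- **That averaging corrupts the musicality result.** It does not. Cancellation concerns the cue ranking only, and only if changes are averaged first, which is the natural reading but is not stated. The Gold-MSI correlation uses participant-level absolute deviations, which cannot cancel.
- **That a null is likely even under a moderate association.** The protocol's own scale calls 0.1 to 0.3 weak and 0.4 to 0.6 moderate. Power at 0.4 is 64% to 70%, so the low power applies to weak relationships.
- **That the plan declares a null to be proof.** The wording is conditional and hedged, and it stands in the Discussion under an exploratory heading. It is not a decision rule.

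**Conclusion.** The point holds for the definitions. The article itself fixes two incompatible adherence scores for the same musicality question, so a separate analysis plan that followed it would inherit the conflict. The primary binary rule credits any overshoot. The practical effect may be negligible or large, because it rests on an assumed distribution of cadence change.

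The Discussion's reading of a null is too strong for this sample: a non-significant result cannot exclude a weak relationship. This rests on 54 to 60 analysed participants, five subscales and the Fisher approximation.

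The ranking rule is a separate, conditional weakness that does not touch objective (b). Its label is also inconsistent with the section Impact of cueing, where effectiveness is judged on gait speed, stride length and stride-time variability and not on cadence matching.

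Severity is minor to moderate, since the objective is secondary and is called exploratory in the Discussion.

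**What to change.** - Use absolute deviation from +10%, per cue, as the adherence measure in the outcome section, the cue ranking and the Gold-MSI analysis.
- Make the binary version a two-sided cut of that measure, for example within 5 points of target, and report overshoot separately. If the 5% threshold is kept, call it cadence response and not adherence.
- Rank cues by mean participant-level absolute deviation, and label the winner best adherence.
- Reword the Discussion: report rho with its confidence interval, and treat a non-significant result as inconclusive about weak associations. An equivalence bound of ±0.3 is not advised. With a half-width of 0.26 to 0.28, it would be met only by an observed rho within about 0.03 to 0.04 of zero.

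The cost is changes to definitions and wording, with no new data. The adherent share may be lower, and the statement about wider applicability becomes weaker.

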### Participants

Sixty (60) PwPD will be recruited for this study, with no specific criteria for recruitment regarding gender or sex.

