#### Sample size.

Sample size calculations were based on detecting changes in gait speed using a within-subject design. Assuming a standardised response mean (SRM) of 0.5 (moderate effect size) for gait speed, a two-sided significance level (α) of 0.01, and 90% power, approximately 54 participants would be required to detect a statistically significant change in gait speed for a single comparison (e.g., cued vs. non-cued walking). When accounting for the three cueing conditions and the associated adjustment for multiple (three) comparisons, we applied a Bonferroni correction resulting in an adjusted alpha of α (0.01/3 = 0.0033). That requirement increases sample size to approx. 55 participants. However, to allow for an anticipated attrition rate of up to 10%, we plan to recruit 60 participants in total. This sample size ensures adequate power to detect moderate cueing effects on gait speed, accommodates potential dropouts, and provides balanced representation across randomisation sequences.

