If assumptions for normality are not met, a Friedman test will be used to assess within-subject differences across cueing conditions. Post-hoc Wilcoxon signed-rank tests, with Bonferroni correction, will be conducted only if the Friedman test is statistically significant. For between-subject effects (e.g., walk order), where normality assumptions are violated, the Kruskal–Wallis test will be used to assess group-level differences between walk-order groups. Interaction effects between cueing and walk order will be explored non-parametrically by conducting separate Friedman tests within each walk order group. Effect sizes for non-parametric tests will be calculated using the rank-biserial correlation coefficient, $\text{r}=\text{Z}/\sqrt{\text{N}}$, providing a measure of the magnitude of the effects observed.

For the three primary comparisons, we will control the familywise error rate using a Bonferroni adjustment. Given three cueing modalities, statistical significance (*p*) will be evaluated at a two-sided α = 0.01/3 = 0.0033. Effect sizes (i.e., SRM) and 95% confidence intervals will also be reported. Secondary and exploratory analyses (e.g., comparing cueing modalities to one another, examining washout effects, assessing stride-to-stride variability) will not be subject to multiplicity correction. For these analyses, a two-sided *p*-value of 0.05 will be considered statistically significant across all parametric and nonparametric tests.

To assess whether the first cue produced short-term residual effects, we will calculate changes in gait outcomes from baseline to each cued walk and from each cued walk to its subsequent washout walk (WO1 and WO2). For each cue exposure, a carryover score will be calculated as the difference between the change induced by the cue and the change observed during the corresponding washout period, reflecting retained cue effects. The approach enables an evaluation of carryover effects after each cued walk separately, thereby capturing any cumulative or progressive retention of cueing effects. Group differences based on initial cue type (i.e., counterbalanced sequence) will be evaluated using one-way ANOVA or the Kruskal–Wallis test, depending on normality assumptions [74–80].

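### The percentage change in cadence is tested against Gold-MSI only after a cut at 5%, which loses power compared with testing the same variable uncut at the same alpha

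*Protocol article*

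**What the plan says.** The Outcome measures section, under Adherence to cues and musicality, declares two forms of adherence: "Adherence will be treated both as a continuous variable (percentage change in cadence from baseline) and as a binary variable for group comparisons". It then fixes the cut: "The primary binary adherence definition is: adherent = ≥5% increase in cadence from baseline; non-adherent = < 5" per cent. The test named there is "Mann–Whitney U tests will compare Gold-MSI between adherent and non-adherent participants". The section gives no source or rationale for 5%, although the cues are set 10% above baseline cadence.

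The last paragraph of the Statistical analysis section adds a correlation analysis: "cue adherence (defined as the absolute deviation from a + 10% target increase in cadence) will be assessed using Spearman’s rank correlation coefficient", Bonferroni-corrected across the Gold-MSI subscales. It also correlates Gold-MSI with changes in gait speed, stride length and stride-time variability.

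For secondary and exploratory analyses in general, the same section removes multiplicity correction and says that "a two-sided *p*-value of 0.05 will be considered statistically significant across all parametric and nonparametric tests". Musicality is secondary objective (b) in the Introduction and appears among the exploratory objectives in the Discussion. The sample size rests on gait speed alone.

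**The concern.** The cut discards information that the trial will hold. A participant at 5.1% is grouped with one at 10% and separated from one at 4.9%. Because the cue aims at +10%, most participants may land on the adherent side. If 91% do, the non-adherent group among 54 participants is about 54 × 0.09 ≈ 5 people.

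The Spearman analysis does not restore this information, because absolute deviation from +10% is a different variable from signed percentage change. A participant at +5% and one at +15% have the same deviation.

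What is at stake is how a null result would be read. The Discussion says that finding no relationship would indicate that the success of music cueing does not depend on musical skill, which would widen its applicability. A null from a test that has discarded information is weak support for that inference.

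**Working it through.** **Inputs from the protocol.** Recruitment: "Sixty (60) PwPD will be recruited for this study". Attrition: "to allow for an anticipated attrition rate of up to 10%, we plan to recruit 60 participants in total", so about 60 × 0.90 = 54 analysed. Two-sided alpha is 0.05 for secondary analyses and the cut is 5%. No power, effect size or adherent share is given for the musicality objective, so there is no figure of the plan's own to reproduce.

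**Assumptions.** Gold-MSI and signed percentage change in cadence are bivariate normal with correlation ρ. The adherent share q follows from the mean and SD of the change: q = Φ((mean − 5)/SD). Means/SDs of 5/4, 7/4, 8/4 and 9/3 per cent give 50%, 69%, 77% and 91%.

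**Step 1: why the cut costs power.** Cutting a normal variable so that a share q lies above c multiplies its correlation with the other variable by φ(c)/√(q(1−q)). The factor is 0.798 at q = 50% and 0.569 at q = 91%. With ρ = 0.4, the correlation left is 0.4 × 0.798 = 0.319 or 0.4 × 0.569 = 0.228.

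**Step 2: approximate power at n = 54, ρ = 0.4.**
- Uncut Spearman: ρs = (6/π)·arcsin(0.4/2) = 0.385. Power ≈ Φ(√(51/1.06) × atanh(0.385) − 1.96) = Φ(0.85) ≈ 80%.
- Mann-Whitney, 50% adherent: Φ(√51 × atanh(0.319) × √(3/π) − 1.96) = Φ(0.35) ≈ 64%.
- Mann-Whitney, 91% adherent: Φ(√51 × atanh(0.228) × √(3/π) − 1.96) = Φ(−0.34) ≈ 37%.

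**Step 3: simulation at n = 54, two-sided 0.05 for both tests (3,000 trials per cell).**

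| ρ | Adherent | Uncut Spearman | Mann-Whitney | Loss (points) |
|---|---|---|---|---|
| 0.4 | 50% | 82% | 64% | 18 |
| 0.4 | 69% | 83% | 60% | 23 |
| 0.4 | 77% | 82% | 55% | 27 |
| 0.4 | 91% | 83% | 36% | 47 |
| 0.3 | 50% | 56% | 40% | 16 |
| 0.3 | 69% | 55% | 36% | 19 |
| 0.3 | 77% | 55% | 34% | 21 |
| 0.3 | 91% | 56% | 21% | 35 |

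A separate simulation with 8,000 runs per cell and adherent shares of 50% to 90% gives losses of 15 to 46 points at n = 54 and 16 to 47 at n = 60. At ρ = 0 each test in the table's simulation holds about 5%.

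**Step 4: outside ρ = 0.3 to 0.4 (n = 60, 50% to 90% adherent).** The loss is 2 to 5 points at ρ = 0.1, 8 to 19 at 0.2, 9 to 39 at 0.5 and 2 to 25 at 0.6.

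**Step 5: does the deviation analysis recover the loss?** At n = 60, ρ = 0.4, an assumed SD of 5 points and uncorrected 0.05:

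| Mean change | Spearman on deviation from +10% | Mann-Whitney on the 5% cut | Spearman on uncut signed change |
|---|---|---|---|
| +5% | 73% | 69% | about 86% |
| +7% | 44% | 66% | about 86% |
| +8% | 25% | 63% | about 86% |
| +10% | 5% | 51% | about 86% |

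For an association with signed change, it does not, and it weakens as the average response nears the target.

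**Step 6: the role of alpha.** Five subscales give 0.05/5 = 0.01. At n = 54 and 0.01 for both tests, ρ = 0.4 gives 61% uncut against 38% at a 50% share and 13% at 90%. If only the Spearman test is held to 0.01, it has about 61% to 62% at ρ = 0.4, against 64%, 60%, 54% and 36% for Mann-Whitney at 0.05. At ρ = 0.3 it has 31% to 34%, against 39%, 37%, 34% and 20%. Most of the gain then disappears unless about 90% adhere.

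**The case against.** **The objective does not rest on the cut test alone.** This stands. The protocol plans an uncut Spearman analysis of Gold-MSI against adherence, and further correlations with gait changes. A reader might infer that musicality is judged only by a dichotomised comparison. The Statistical analysis section rules that out. What remains is narrower: the percentage change, which the protocol itself declares continuous, is never tested uncut.

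**Signed change may not be the better target.** This stands in part. Signed change ranks a participant at +18% above one exactly on the +10% beat, whereas the Statistical analysis section treats the change closest to 10% as best. The simulations assume that Gold-MSI rises linearly with signed change, which favours the uncut signed test. However, the 5% cut is itself a cut of signed change, and it also counts overshoot as adherence. Comparing it with the same variable uncut is therefore like with like.

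**A corrected Spearman test would gain little over an uncorrected Mann-Whitney test.** This stands, as Step 6 shows. It limits how the fix may be worded. It does not make the cut efficient, since at equal alpha the uncut test had more power in every simulated cell.

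**The objective is minor.** This stands. It is secondary, labelled exploratory in the Discussion, and the trial was not sized for it. A fixed-threshold comparison beside a continuous analysis is suboptimal rather than invalid.

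**Conclusion.** The point holds in a limited form. The protocol tests percentage change in cadence against Gold-MSI only after a cut with no stated source, and its uncut analysis uses a different variable. At equal alpha the cut costs power.

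The loss is about 16 to 47 points if ρ is 0.3 to 0.4 and 50% to 91% adhere, with 54 to 60 participants and two-sided 0.05. Over ρ of 0.1 to 0.6 it is about 2 to 47 points. These figures rest on bivariate normality, a linear relation with signed change and an assumed adherent share.

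A reader might take 16 to 47 points as a property of this plan. The documents do not support that, because they give neither the correlation nor the adherent share. The top of the range needs about 90% adherent. No primary result is affected.

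**What to change.** In the Outcome measures section, under Adherence to cues and musicality:

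- Replace the Mann-Whitney test, for each cue, with a Spearman correlation and 95% CI of Gold-MSI against the uncut percentage change in cadence.
- Use the same alpha that the Mann-Whitney test would have had. Any correction across subscales should apply equally whichever test is used.
- Keep the analysis of absolute deviation from +10% in the Statistical analysis section.
- Report the 5% split descriptively: number and percentage adherent per cue and median Gold-MSI by group, with no p-value.

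This changes wording only and needs no new data or visits. There are two costs. The p-value for the simple adherent versus non-adherent contrast is lost. Signed change also counts overshoot beyond +10% as greater adherence, so its result should be read beside the deviation analysis.
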